# The effects of low-intensity blood flow restricted exercise compared with conventional resistance training on the clinical outcomes of active UK military personnel following a 3-week in-patient rehabilitation programme: protocol for a randomized controlled feasibility study

**DOI:** 10.1186/s40814-017-0216-x

**Published:** 2017-12-08

**Keywords:** Blood flow restriction, Musculoskeletal rehabilitation, Lower-limb, Muscle, Strength, Hypertrophy, Pain

## Abstract

**Background:**

A challenge for rehabilitation practitioners lies in designing optimal exercise programmes that facilitate musculoskeletal (MSK) adaptations whilst simultaneously accommodating biological healing and the safe loading of an injured limb. A growing body of evidence supports the use of resistance training at a reduced load in combination with blood flow restriction (BFR) to enhance hypertrophic and strength responses in skeletal muscle. In-patient rehabilitation has a long tradition in the UK Military, however, the efficacy of low intensity (LI) BFR training has not been tested in this rehabilitation setting. The aims of this study are to determine (1) the feasibility of a randomised controlled trial (RCT) investigating LI-BFR training in a residential, multidisciplinary treatment programme and (2) provide preliminary data describing the within and between-group treatment effects of a LI-BFR intervention and a conventional resistance training group in military personnel.

**Methods:**

This is a single-blind randomised controlled feasibility study. A minimum of 28 lower-limb injured UK military personnel, aged 18 to 50 years, attending rehabilitation at the UK Defence Medical Rehabilitation Centre (DMRC) will be recruited into the study. After completion of baseline measurements, participants will be randomised in a 1:1 ratio to receive 3 weeks (15 days) of intensive multidisciplinary team (MDT) in-patient rehabilitation. Group 1 will receive conventional resistance training 3 days per week. Group 2 will perform twice daily LI-BFR training. Both groups will also undertake the same common elements of the existing MDT programme. Repeat follow-up assessments will be undertaken upon completion of treatment. Group 2 participants will be asked to rate their pain response to LI-BFR training every five sessions.

**Discussion:**

The results will provide information on the feasibility of a full-scale RCT. Recommendations for an adequately powered study to determine the efficacy of LI-BFR training during in-patient rehabilitation can then be made. The study may also provide insights into the potential effectiveness of LI-BFR training as a novel exercise modality to induce muscle adaptations in the absence of high mechanical loading of the lower-limb.

**Trial registration:**

ISRCTN Reference: ISRCTN 63585315 dated 25 April 2017.

## Background

The maintenance of adequate skeletal muscle is crucial for maintaining the ability to undertake activities of daily living, ambulation, falls avoidance and general health [1]. Disuse of skeletal muscle, often associated with musculoskeletal (MSK) injury, can lead to relatively rapid and progressive atrophy; shortening of muscle fibres, decreased oxidative capacity, and reduced muscle compliance [2]. It is widely acknowledged that muscle atrophy can prolong the duration of MSK rehabilitation, increase the cost to health care providers and prevent optimal recovery [3]. Thus, strategies to increase or maintain muscle tissue across the lifespan are crucial for overall health and quality of life.

The goal of the surgical and rehabilitative team focuses on the safe return of a patient to their previous level of function. MSK rehabilitation can be considered in terms of the appropriate integration and progression of the following broad exercise components: endurance, flexibility, proprioception, balance, joint and soft tissue mobility, speed and power [4]. Strength training is most closely associated with improvements in functional ability during rehabilitation [5]. Therefore, maximising the potential for adaptations in muscle strength is a crucial factor in the progression of any MSK exercise rehabilitation programme. A significant challenge lies in designing optimal rehabilitation programs that facilitate both neurological and muscular adaptations whilst accommodating biological healing and patient safety [4]. Historically, it has been widely accepted that to elicit significant gains in muscle hypertrophy and strength requires loads equivalent to at least 70% of an individual’s 1 repetition maximum (1RM) for a given movement [6, 7]. For people undergoing musculoskeletal injury rehabilitation, heavy-load resistance training can be contraindicated [2] or they are limited by their symptomatic impairment, including pain and immobility, to attain the recommended heavier-loads [8]. Therefore, patients with MSK injuries are often advised to reduce their training load, potentially limiting the desired muscular response to treatment.

In recent years, research demonstrates that the use of blood flow restriction (BFR) combined with low-load resistance exercise (20–40% 1RM) can enhance the morphology and strength response in human muscle tissue [9]. BFR is typically achieved via a pressurised cuff [10], tourniquet [11] or elastic banding [12]. The external pressure applied to the proximal portion of the upper or lower extremities should be low enough to maintain partial arterial inflow into the muscle, but high enough to occlude venous return from the muscle [13]. During periods of immobilisation, the application of BFR alone has been shown to reduce muscular atrophy [14]. However, to optimise muscular development, BFR must be combined with an exercise stimulus (aerobic conditioning or resistance training), with the greatest muscle strength and morphological responses achieved when BFR is combined with resistance training [2].

When supervised by experienced practitioners, low-intensity BFR (LI-BFR) has been shown to be a safe and effective tool to improve strength and function in athletes [15], the elderly [16, 17] healthy adults [18] and during MSK rehabilitation [19–24]. Additional benefits reported with LI-BFR training, is the potential for increases in muscle hypertrophy and strength in muscles located proximal to the applied pressure (i.e. muscles not direct under BFR) as a result of pre-fatigue of the muscles below the cuff [25]. It is possible that this additional muscle stimulus proximal to the cuff (e.g. in the Gluteus Maximus muscle during a squat or leg press) may further enhance physical function and accelerate progression during MSK rehabilitation. Adverse events to acute sessions of LI-BFR have been reported and primarily include delayed onset of muscle soreness, numbness, fainting/dizziness and bruising [26]. There have also been case study reports of rhabdomyolysis [27, 28] and retinal occlusion [29] in the literature. However, when appropriately supervised, LI-BFR is widely acknowledged as a safe mode of exercise in healthy adults [30].

It is proposed that the metabolic stress associated with BFR and the mechanical tension of the load lifted act synergistically to mediate numerous secondary mechanisms, all of which stimulate autocrine and/or paracrine actions to facilitate muscle growth [31]. These proposed mechanisms include muscle cell swelling [32], elevated systemic hormone production [33, 34], intramuscular anabolic/anti-catabolic signalling [35–37], increased fast twitch fibre recruitment [38] and the production of reactive oxygen species (ROS) [39, 40] and its variants, including i) nitric oxide for its influence on vascular responses [41, 42] and ii) some heat shock proteins [36, 39]. However, in the absence of research demonstrating a causal link, any suggested associations between BFR training and subsequent muscle growth are purely speculative.

There is increasing evidence for the practical and beneficial use of BFR training as a clinical MSK rehabilitation tool [43]. Any intervention that speeds the progression of MSK rehabilitation, whilst exercising at lower relative training loads, is of interest not only to the rehabilitation and sports medicine communities, but the wider community health services. In military populations, the majority of injuries occur in the lower limb [44]. In a cohort of 6608 British Army recruits, during a 26-week period of initial military training, the overall incidence of musculoskeletal injuries was 48.6% [45]. There is a large economic and operational cost associated with lower-limb MSK injury. Soldiers injured during basic training, field exercise, sport etc. may be unable to deploy on operations, whilst soldiers injured during deployment may not be fit to return to active duty [44]. The Centre for Lower-Limb Rehabilitation at the UK Defence Medical Rehabilitation Centre (DMRC), Headley Court routinely treats and manages a large variety of lower-limb musculoskeletal disorders (See Fig. 1 for a diagrammatic model of the rehabilitation pathway). These typically include, but are not limited to, overuse injuries (e.g. patellofemoral pain, tendinopathy, early osteoarthritis, and exertional lower-limb pain), post-surgical injuries (e.g. soft-tissue and ligamentous reconstruction), bone fractures, and hip and groin pain.

**Fig. 1 Fig1:**
[figure not shown]
Lower limbs rehabilitation pathway at DMRC, Headley Court

Of particular interest, in relation to the UK military model of exercise rehabilitation (Fig. 1), is the evidence of muscular hypertrophy and strength demonstrated with high frequency (twice a day) BFR training in as little as 6 days [46] and 12 days [47] of training. The effect of this novel training method is yet to be explored across the UK Defence Medical Services (DMS). Therefore, the purpose of this study is to assess the feasibility of LI-BFR training in a heterogeneous group of lower-limb injured military personnel, under the conditions provided during a 3-week intensive residential rehabilitation centre. This includes measuring the hypertrophic and strength response but also reporting any potential adverse events, monitoring compliance and the pain response over time and whether frequent daily use of this clinical tool is feasible in a busy MDT clinical rehabilitation setting where other potentially conflicting clinical priorities exist. This protocol describes the design and analysis plan for a randomised controlled feasibility study.

## Methods/design

The primary aim of this study is:To assess the acceptability, feasibility and adverse events associated with implementing a high-frequency LI-BFR intervention in a 3-week intensive residential MDT rehabilitation setting.To assess the feasibility of a future definitive RCT by assessing participant eligibility, monitoring recruitment and retention rates, group allocation acceptance and adherence to the intervention.

The secondary aim is to compare the effects of LI-BFR training against conventional resistance training on cross-sectional area (CSA) and volume of the quadriceps and hamstring muscle groups and muscle strength in UK military personnel undergoing lower-limb injury rehabilitation. Changes in relevant musculoskeletal variables of treatment routinely measured as part of the standard UK military rehabilitation care pathway will also be assessed. This includes walk/run assessment, balance, pain perceptions and compliance to the exercise rehabilitation programme.

### Study design

This is a parallel group, two-arm, assessor-blinded randomised controlled feasibility study. It is a two (group) by two (time) repeated measures design. Outcome measurements will be assessed at baseline and 3-weeks. The study protocol has been developed in accordance with the Standard Protocol Items: Recommendations for Interventional Trials (SPIRIT) guidelines [48]. The overall study design is illustrated in Fig. 2.

**Fig. 2 Fig2:**
[figure not shown]
Study design

### Setting

The study will be conducted at a specialist UK military rehabilitation centre.

### Ethics

The study was reviewed and approved by the UK Ministry of Defence (MOD) research ethics committee (study reference protocol number: 442/MODREC/13). Any requirement for protocol modifications will be submitted for authorisation to the MOD research ethics committee.

### Study participants

We will recruit a minimum of 28 participants aged 18-50 years admitted for treatment to the Centre for Lower-Limb Rehabilitation (Defence Medical Rehabilitation Centre (DMRC), Headley Court, UK) with a MSK injury of the lower limb. Table 1 describes the inclusion and exclusion criteria. These criteria are designed to recruit a heterogeneous group of lower-limb injured patients who are able to engage in load bearing conventional resistance training, but do not have a functional status allowing a return to full operational military duties. A significant majority of patients admitted to DMRC for rehabilitation are male. In a ‘time limited’ period allocated for data collection, we could not predict the number of females available for recruitment into the study. Therefore, because the primary purpose of this study is to assess the feasibility and not the effectiveness of the LI-BFR intervention, for ease of administration and logistics, we chose to recruit males only. If feasible, any future full-scale RCT will recruit both male and female participants.

**Table 1 Tab1:** Study inclusion and exclusion criteria

Inclusion criteria
1. Male
2. 18 to 50 years of age
3. Serving regular UK Armed Forces personnel
4. Lower limb injury (e.g. patellofemoral pain, ACL reconstruction, ankle injury, projectile/blast related injury)
5. Referred to Defence Medical Rehabilitation Centre (DMRC), Headley Court for treatment.
6. Present with a level of function enabling engagement in conventional load bearing exercise rehabilitation confirmed by clinical assessment findings and recent training history.
7. Unable to return to active duty due to physical impairment and occupational limitations (e.g. medical downgrading).
Exclusion Criteria
1. Female
2. History of cardiovascular disease (hypertension, peripheral vascular disease, thrombosis/embolism, ischaemic heart disease, myocardial infarction)
3. History of the following musculoskeletal disorders: rheumatoid arthritis, avascular necrosis or osteonecrosis, severe osteoarthritis
4. History of the following neurological disorders: Peripheral neuropathy, Alzheimer’s disease, amyotrophic lateral sclerosis, multiple sclerosis, Parkinson’s disease, stroke, mild or severe traumatic brain injury
5. Chronic or relapsing/remitting gastrointestinal disorders such as inflammatory bowel diseases, irritable bowel syndrome or gastrointestinal infections within 28 days of screening.
6. Acute viral or bacterial upper or lower respiratory infection at screening
7. Moderate or severe chronic obstructive pulmonary disease (COPD)
8. Amputation to the lower or upper extremity
9. Known or suspected lower limb chronic exertional compartment syndrome (CECS) (tourniquet raises intra-compartmental muscle pressure)
10. Achilles or patella tendinopathy (slow heavy resistance or eccentric exercise programme prescribed as evidence-based for confirmed tendinopathy diagnosis)
11. ACL surgery within the last 4 weeks
12. Surgical insertion of metal components in lower limbs (may affect MRI results)
13. History of any of the following conditions or disorders not previously listed: diabetes, fibromyalgia, active cancer, severe obesity (i.e., body mass index greater than 35 kg/m^2^), diagnosed mental illness (e.g. PTSD, depression, anxiety)
14. Current or previous use of any drugs known to influence muscle mass or performance within previous 6 months
15. Elevated risk of unexplained fainting or dizzy spells during physical activity/exercise that causes loss of balance

### Randomisation and blinding

Potential participants will be referred from their parent military unit by a physiotherapist or medical officer. Prior to admission to DMRC, the case records of individual patients scheduled for a lower-limb rehabilitation course will be reviewed by a specialist rehabilitation consultant ([name]). Those who meet the preliminary inclusion criteria will be contacted via telephone by a member of the research team to discuss their possible inclusion in the study. Potential participants will be sent an information pack consisting of the patient information sheet (PIS) and an accompanying consent form. Upon admission to DMRC Headley Court, potential participants will undertake a comprehensive musculoskeletal examination by a specialist consultant and experienced musculoskeletal physiotherapist where a secondary screening will confirm the patient’s eligibility to enter the study. Participants meeting the eligibility criteria, who have read and understood the PIS and volunteer to participate will return a signed informed consent form, before being randomly assigned to one of the two study groups. A block randomisation method will be used to randomise participants into groups that result in equal sample sizes. Our decision to employ a simple form of block randomisation is because (a) we want to ensure an equal number of participants are assigned to each group during a finite, time-limited period for data collection, (b) we already have a homogenous participant group with standardised prognostic factors, and (c) we will not be undertaking formal statistical testing. A plain language statement will inform participants that they have an equal chance of receiving the LI-BFR or conventional resistance training intervention. A sealed envelope will be opened to reveal group allocation by an independent administrator not involved in the recruitment, treatment or assessment of study outcomes. Group allocation will be documented and communicated to the supervising therapists by the independent administrator. Prior to the study, all treating staff will have received a briefing on the randomisation process and specific intervention for each treatment group, in line with the study protocol. It is not possible to blind participants to treatment allocation in this study. The clinical staff supervising both groups will be, by necessity, un-blinded. We will use trained blinded outcome assessors to measure and record the outcome scores in this study. A diagrammatic description of the study design can be found in Fig. 2.

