### Statistical analyses

Data generated from this pilot study will help inform a future fully-powered RCT by testing the study procedures. We will not use feasibility trial data to formally test for between-group differences, and the analysis will be of a descriptive nature. Therefore, no statistical analyses will be performed for the pilot data. Descriptive statistics (mean, standard deviation (SD), counts (percentage)) will be used to summarise eligibility, consent, randomisation, adverse events, retention, completion and intervention adherence rates. Description of participant demographic and baseline characteristics will be compared and simple tabulation of this pilot data will be presented. The 95% confidence intervals will be calculated to inform a sample size for a future definitive RCT. All participants will be included in the analysis. This statistical analysis of the pilot data will be exploratory only as our sample size will not allow for a definitive analysis. We will recommend progression to a full study application if minimum criteria are reached in key feasibility aims and objectives. These criteria will include a minimum 80% of target participant recruitment over a 6-month period, and a minimum 80% completion of the LI-BFR intervention and outcome measurement.

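### Simple block randomisation is defended partly by a homogeneous sample that the protocol sets out not to recruit, and the analysis section does not say what its confidence intervals will estimate

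*Protocol article*

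**What the plan says.** Under Randomisation and blinding, the protocol article gives three reasons for a simple form of block randomisation. Reason (a) is that the arms should come out the same size although the window for collecting data is short. Reason (b) is that "we already have a homogenous participant group with standardised prognostic factors". Reason (c) is that no formal tests are planned. No stratification factor is named.

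The population is described differently elsewhere. The last paragraph of the Background says the purpose is to "assess the feasibility of LI-BFR training in a heterogeneous group of lower-limb injured military personnel". Study participants says "These criteria are designed to recruit a heterogeneous group of lower-limb injured patients". The injury criterion in Table 1 begins "Lower limb injury (e.g. patellofemoral pain, ACL reconstruction, ankle injury, projectile/blast related injury", and the age range is 18 to 50 years.

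On analysis, the Abstract promises preliminary data on within-group and between-group treatment effects. Methods/design makes comparison of the two trainings on muscle size and strength the secondary aim. Statistical analyses first excludes formal between-group testing and calls the analysis descriptive. It then says "Therefore, no statistical analyses will be performed for the pilot data", and a little later "The 95% confidence intervals will be calculated to inform a sample size for a future definitive RCT". Sample size sets 14 per arm, hopes for at least 12 per arm with full data, and says the sample will inform a power analysis for the full trial.

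**The concern.** Reason (b) is contradicted by the article's own description of its patients, and nothing in Table 1 standardises prognosis. Reason (c) is true, but it does not make imbalance harmless: a chance difference in prognosis moves an estimate whether or not anyone tests it, and estimates are promised.

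The analysis wording adds to the difficulty. A plan cannot both perform no statistical analysis and produce confidence intervals that feed a sample-size calculation. The article does not say whether those intervals are for feasibility rates, group means, between-group differences or SDs. What is at stake is how the preliminary between-group results are read, and which quantity is carried into the design of the definitive trial.

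**Working it through.** **1. The plan's own figure.** 2 × 14 = 28 reproduces. Keeping 12 of 14 per arm allows a loss of 1 − 12/14 = 14.3%. The article gives no alpha, power, effect or SD, so there is no power figure to check.

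**2. Chance imbalance in one continuous baseline variable, in SD units.** The standard error is √(2/n).

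| Per arm | Standard error | 95% range (1.96 × SE) | Chance of exceeding 0.5 SD |
|---|---|---|---|
| 14 | √(2/14) = 0.378 | ±0.74 | 18.6% |
| 12 | √(2/12) = 0.408 | ±0.80 | 22.1% |

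**3. Chance imbalance in a binary factor.** Assume it is present in 14 of 28 patients; the article gives no prevalence. By the hypergeometric distribution, a split of 9:5 or worse has probability 25.7%, and 10:4 or worse 5.7%.

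**4. Effect on the unadjusted difference.** This was simulated with 60,000 trials per scenario, 14 per arm, total SD 1, and the factor assumed to explain 10%, 25% or 40% of outcome variance.

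- Over all randomisations the mean difference is 0.00 and its SD about 0.38.
- In trials with a 10:4 or worse split, the difference shifts by about 0.29, 0.46 or 0.57 SD respectively.
- Stratifying on that factor would lower the SD of the difference to about 0.36, 0.33 or 0.29.

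**5. Effect on the within-arm SD.** Without stratification the mean pooled variance is 1.00 to 1.02. In the badly imbalanced trials it is 0.94 to 0.98, and √0.944 = 0.97, so the SD changes by at most about 3%. Ordinary sampling error of an SD on 26 degrees of freedom has a 95% range of about −21% to +37%.

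**6. Precision of a pilot effect.** The 95% confidence half-width is t(0.975, 26) × 0.378 = 0.78 SD with 14 per arm, and 0.85 SD with 12. If an observed effect were used for sizing at 80% power and two-sided 5%, the number per arm would be 175 at 0.3 SD, 63 at 0.5 SD and 33 at 0.7 SD. An estimate this imprecise cannot set the design, with or without stratification.

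**7. What baseline adjustment buys.** Let r be the baseline/follow-up correlation (assumed) and take equal SDs at both times. Relative variances are 1 for raw follow-up values, 2(1 − r) for change scores and 1 − r² for ANCOVA.

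| Assumed r | Raw / ANCOVA = 1/(1 − r²) | Change / ANCOVA = 2/(1 + r) |
|---|---|---|
| 0.5 | 1.33 | 1.33 |
| 0.8 | 2.78 | 1.11 |
| 0.95 | 10.3 | 1.03 |

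**The case against.** The case for leaving the plan alone is strong in several respects.

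- Reason (a) supports simple blocks without help from (b). Stratified blocks in 28 patients can end incomplete and work against equal arms. This stands, and it is why stratification is only optional.
- The sentence ruling out statistical analyses follows one about formal between-group tests, so its likely meaning is that no tests will be done. This is a fair reading, but the text should say so, and it still does not tell the reader what the intervals estimate.
- The article is a condensed document, and an analysis plan not shown may specify the estimator. That is a reason not to treat silence on adjustment as an error. It does not reconcile sentences that conflict within the article.
- The analysis is labelled exploratory, and the feasibility aims and the 80% progression criteria do not depend on this comparison. This stands.

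A reader might infer more than the text supports:

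- **That adjustment is waived because the group is thought homogeneous.** The three reasons concern the randomisation method only; adjustment is not mentioned.
- **That baseline values will go unused.** The two-by-two repeated-measures design, the assessment of changes and the promised within-group effects all use them.
- **That imbalance corrupts the SDs used for sizing.** Step 5 shows it hardly touches them.
- **That the next trial would be oversized 2.8 to 10 times.** This needs sizing from raw follow-up SDs at r of 0.8 to 0.95, which is nowhere stated. Against change scores, which fit the text better, the excess is about 3% to 11% at the same r.
- **That the pilot effect will be the design effect.** The article says only that the sample and the intervals will inform sizing.

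**Conclusion.** The contradiction holds. Homogeneity is given as a reason for simple blocks in a trial designed to recruit a heterogeneous group. The analysis section also conflicts with itself over whether any analysis is done, and leaves its confidence intervals undefined.

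The consequence is moderate and limited. In a single trial of this size, chance imbalance can be large: ±0.74 SD at the 95% level for each baseline variable, and beyond 0.5 SD in about one trial in five. It is imprecision in one small trial, not systematic bias. It bears on the secondary between-group comparison alone.

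The imbalance figures in step 2 need only the stated arm sizes. Steps 3 and 4 depend on an assumed prevalence and prognostic strength, and step 7 on an assumed correlation. Adjusting for the baseline value removes imbalance in that value. It removes imbalance in injury type or age only so far as these act through it.

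**What to change.** 1. In Randomisation and blinding, correct reason (b) so that it agrees with the Background, Study participants and Table 1. Rest the simple blocks on reason (a). Reason (c) may stay as a statement of fact, but not as grounds for disregarding imbalance.
2. In Statistical analyses, replace the sentence excluding all statistical analyses with one excluding hypothesis tests, and name the quantities for which 95% confidence intervals will be given.
3. For each secondary outcome measured at baseline and 3 weeks in both groups, report the between-group difference with its 95% confidence interval from an ANCOVA on the baseline value, together with the residual SD and the baseline/follow-up correlation.
4. State that the definitive trial will be sized from a clinically important difference and that residual SD, allowing for the SD's uncertainty, and not from the observed pilot effect.
5. Optionally, if allocation envelopes are not yet prepared, stratify the blocks on one prognostic factor that covers every injury type admitted.

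Items 1 to 4 cost some rewording and one short regression per outcome. Outcome measures already provides for baseline and 3-week assessment, so no new data are needed and the sample stays at 28. Item 5 would mean preparing the envelopes again.
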